#### Supplemental analysis

We will explore whether the effect of implementation strategies on student outcomes differ by 1) autistic students versus classmates who are peripheral/isolated on their social network; and 2) demographic characteristics (e.g., age, gender, and race/ethnicity) by extending the moderation analysis in Secondary Aim 3.

#### Missing data

For modeling and hypothesis testing, the proposed likelihood-based approach regards missing data as missing at random (MAR; i.e., missing data are independent of unobserved data). The likelihood-based solutions are robust to violations of ignorable missing data (i.e., situations where the MAR assumption is not met) [79]. We will examine the degree of randomness in missing data by comparing the frequency, reasons, pattern, and time to dropout and missing values across strategies. Missing data will use multiple imputation [80]. In sensitivity analyses, all aims will be analyzed with and without the multiple imputed data.

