#### Inclusion/exclusion

We will recruit *n* = 121 educators who attend recess and are school district employees, to ensure they have the capacity to participate in research activities. We also will recruit *n* = 55 general and/or special education teachers to complete study measures about students and school-level constructs and *n* = 83–138 other school personnel (e.g., administrators, teachers) to serve on the school-based teams (approximately 3–5 participants). Participants will remain in the study for 18 months unless they withdraw or change jobs. School personnel involved with *RR* coaching will receive $50 for their data completion. School personnel involved with school-based teams will receive $25 per session and $25 for their data completion. Teachers will receive $25 for their data completion and an additional $10 per student per data collection timepoint.

We will recruit 118 autistic students and allistic classmates. Autistic students will be included if they: 1) have a documented autism classification; 2) are between the ages of 5–12 and enrolled in Kindergarten through 5th grade; and 3) share a recess period with allistic peers. Allistic classmates will be included if they are: 1) isolated or peripheral on their classroom social network; and 2) require support during recess. Autistic students and their peers without an available educator supporting recess will be excluded. Participants will not be excluded given their sex, gender identity, age, or racial/ethnic background, and will not be asked to disrupt any other service utilization.

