#### Sample size and power considerations

The sample size for the study (*n* = 121 educators, *n* = 118 students in *n* = 55 elementary schools) was determined based on statistical power for the Primary Aim 1 contrast, a between implementation strategies (coaching with school-based teams vs. coaching only) mean comparison in change in *RR* fidelity (primary outcome) from T1-T3. Based on a Type-I error rate of 5%, a within-person correlation in paraeducator fidelity of ICC = 0.36 (based on preliminary data), a total number of 98 educators are needed to detect a difference of at least 0.15 in the comparison of slopes in educator’s *RR* fidelity with 80% power. After accounting for an estimated attrition rate of 10% and a 10% variance inflation factor for clustering by school, a total number of *N* = 121 is needed. Similarly, for our Primary Aim 1 secondary outcome, peer engagement, assuming a Type-I error rate of 5%, a within-person correlation in students’ joint engagement of ICC = 0.18 (based on preliminary data), a total number of 118 students are needed to detect a difference of at least 14% in total time spent in joint engagement in the comparison of slopes in joint engagement between coaching with school-based teams vs. coaching only with 80% power and 10% attrition and 10% variance inflation factor for clustering by school.

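### The Missing data section wrongly says likelihood methods are robust when MAR fails, and the sensitivity analysis it describes would not show how far informative loss could move the result

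*Protocol article*

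**What the plan says.** The Missing data section of the protocol article makes five statements in sequence.

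- It names the assumption: "the proposed likelihood-based approach regards missing data as missing at random (MAR; i.e., missing data are independent of unobserved data".
- It then says the assumption is not needed: "The likelihood-based solutions are robust to violations of ignorable missing data (i.e., situations where the MAR assumption is not met".
- It plans a descriptive check: "We will examine the degree of randomness in missing data by comparing the frequency, reasons, pattern, and time to dropout and missing values across strategies".
- It plans multiple imputation, citing a reference but naming no mechanism, variables or model.
- It defines the sensitivity analysis: "In sensitivity analyses, all aims will be analyzed with and without the multiple imputed data".

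The other sensitivity analyses in the article, under Cost and cost-effectiveness analysis, concern cost estimates and the ICER.

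Data can be lost in ways the article itself describes. Under Inclusion/exclusion: "Participants will remain in the study for 18 months unless they withdraw or change jobs". Under Data collection, year-two coding of fidelity and peer engagement depends on the student still being at the school. Under Limitations, the authors expect that remote coaching may raise attrition.

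**The concern.** The second statement contradicts the first. If the method rests on MAR, failure of MAR is the situation in which it loses its guarantee. The parenthesis in the quoted sentence spells out MAR failure, so no milder reading is available.

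The practical risk lies in interpretation. A team that believes the model is robust, and then sees similar results with and without imputation, may report the fidelity result as robust to drop-out when neither analysis has addressed informative drop-out. The trial's own theory makes such loss plausible. School leadership and climate are held to drive use of the intervention, only one arm targets them, and educators in unsupportive schools may be more likely to leave. Sustainment is more exposed than fidelity, because it is measured only at T4 and T5 and has no earlier score on the same scale from which to predict a missing one.

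**Working it through.** **1. The plan's own figure.** Attrition enters the plan numerically only through the sample size: "a total number of 98 educators are needed to detect a difference of at least 0.15 in the comparison of slopes in educator’s" fidelity with 80% power, then "After accounting for an estimated attrition rate of 10% and a 10% variance inflation factor for clustering by school, a total number of" 121. This reproduces: 98 / (0.90 × 0.90) = 120.99, rounded up to 121. Nothing in this point changes that number.

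**2. What drives bias.** Let p be the proportion missing in an arm and d the MAR-predicted mean minus the true mean of those missing.

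- Bias in an arm mean = p × d.
- Bias in the arm contrast = p(teams) × d(teams) − p(coaching) × d(coaching).

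If p and d are equal in both arms, the contrast is unbiased, although the change within each arm is not. If either differs, the contrast is generally biased. The article gives no p by arm and no d.

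**3. Would the planned comparison show it?** This was checked by simulation. The inputs were:

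- From the article: three visits (T1–T3, the period used for the sample size), correlation 0.36, true difference 0.15.
- Back-solved, because no SD is given. With two-sided 5% and 80% power, the SD of change is 0.15 / [(1.960 + 0.842) × √(4/98)] = 0.265. The single-visit SD is 0.265 / √(2 × (1 − 0.36)) = 0.234. Here the 0.15 slope difference is treated as a difference in T1–T3 change.
- Assumed: T3 drop-out with log-odds 1.5 per SD, lower scorers leaving more often. Under MAR it depends on the observed T2 value; under informative loss, on the unseen T3 value. Where only one arm is informative, it is coaching only, and loss in the teams arm is random.
- Estimators: normal maximum likelihood, and multiple imputation from the same variables.

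| Loss: coaching only, teams | Mechanism | Likelihood | Imputation | Bias |
|---|---|---|---|---|
| 10%, 10% | MAR | 0.1493 | 0.1493 | −0.5% |
| 10%, 10% | informative, same in both arms | 0.1494 | 0.1493 | −0.4% |
| 10%, 10% | informative, one arm | 0.1264 | 0.1264 | −15.8% |
| 20%, 10% | MAR | 0.1495 | 0.1494 | −0.3% |
| 20%, 10% | informative, both arms | 0.1295 | 0.1295 | −13.7% |
| 20%, 20% | informative, same in both arms | 0.1502 | 0.1504 | +0.1% |
| 30%, 10% | informative, both arms | 0.1092 | 0.1094 | −27.2% |
| 30%, 10% | informative, one arm | 0.0846 | 0.0844 | −43.6% |

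The two methods agree to within 0.0002 in every row, whether unbiased or biased.

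**4. Cross-check against step 2.** At 10% loss per arm, informative in one arm, the bias is 0.1500 − 0.1264 = 0.0236, so d = 0.0236 / 0.10 = 0.236. The residual SD at T3 given T1 and T2 is 0.234 × √(1 − 2 × 0.36² / 1.36) = 0.211. The assumed mechanism therefore puts leavers about 0.236 / 0.211 = 1.1 residual SDs below prediction, which is a fairly strong departure from MAR.

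**The case against.** Four objections carry weight, and each limits how far the point can be taken.

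- **A reader might infer that informative drop-out is never tested in this trial.** The documents do not support that. Only a condensed article is at hand, and an MNAR analysis may well sit in an analysis plan that is not shown. What can be said is that none is described here. The incorrect sentence is different: it is a positive statement, not an omission.
- **A reader might infer that results with and without imputation must agree.** That holds only if imputation uses the same variables as the GLMM, as in the simulation. The fidelity GLMM adjusts for site and years of experience, but leadership, climate and acceptability are collected at T1–T5. If these enter the imputation model, loss driven by poor school support could be closer to MAR and the two analyses could differ informatively. They would still share an MAR assumption.
- **A reader might attach a fixed size to the bias, such as one fifth or one third of the 0.15 target.** Such figures need drop-out rates by arm and shortfalls among leavers that the article does not give, and they set a bias in an arm mean against a difference in slopes. The fidelity scale is also unsettled: a proportion in Table 2, a component count and a 1–5 quality mean under Implementation outcomes.
- **The plan has real safeguards.** It commits to collecting outcomes from participants who do not engage. Not using the intervention is scored, not missing. The planned review of reasons for and timing of drop-out is useful. It cannot separate MAR from MNAR, however, nor show how far the estimate could move.

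**Conclusion.** The robustness sentence is wrong as published, contradicts the sentence before it, and should be corrected whatever the full analysis plan contains. The sensitivity analysis described in this document, on its natural reading as standard imputation, stays under MAR, so agreement with the likelihood result would not be evidence of robustness to informative loss. That reading is an inference, because the article names no imputation mechanism.

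Bias in the arm contrast is possible but not inevitable. It was about zero when loss and mechanism were equal in both arms, and −14% to −44% of the 0.15 effect in the arm-differential rows shown. Those sizes rest on the assumed drop-out model and back-solved SD and are illustrations only. The direction is not fixed either: in the table, poor performers are lost mainly from coaching only, which dilutes the effect; the same loss mainly from the teams arm would inflate it.

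**What to change.** 1. Delete the robustness sentence, or replace it with a statement that both the GLMM and multiple imputation are valid under MAR, given the observed data and a correct model.
2. Keep the comparison with and without imputation, and put the leadership, climate and acceptability measures already collected into the imputation model. Leadership and climate are aggregated to school level, so ratings by remaining staff can still inform the imputation after one educator leaves.
3. Add a delta-adjusted (pattern-mixture) analysis for the primary fidelity contrast and for sustainment. Shift imputed values over a stated range, separately by arm, and report the shift at which the conclusion changes. State the range on the fidelity scale finally chosen.

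Scoring educators who leave as not using the intervention is not part of this correction. It answers a different question and is an optional choice of estimand.

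The cost is a wording change and modest extra programming. Sample size and data collection are unaffected, and the article reports no enrolment as of September 2024.

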#### Sample size and power considerations

The sample size for the study (*n* = 121 educators, *n* = 118 students in *n* = 55 elementary schools) was determined based on statistical power for the Primary Aim 1 contrast, a between implementation strategies (coaching with school-based teams vs. coaching only) mean comparison in change in *RR* fidelity (primary outcome) from T1-T3. Based on a Type-I error rate of 5%, a within-person correlation in paraeducator fidelity of ICC = 0.36 (based on preliminary data), a total number of 98 educators are needed to detect a difference of at least 0.15 in the comparison of slopes in educator’s *RR* fidelity with 80% power. After accounting for an estimated attrition rate of 10% and a 10% variance inflation factor for clustering by school, a total number of *N* = 121 is needed. Similarly, for our Primary Aim 1 secondary outcome, peer engagement, assuming a Type-I error rate of 5%, a within-person correlation in students’ joint engagement of ICC = 0.18 (based on preliminary data), a total number of 118 students are needed to detect a difference of at least 14% in total time spent in joint engagement in the comparison of slopes in joint engagement between coaching with school-based teams vs. coaching only with 80% power and 10% attrition and 10% variance inflation factor for clustering by school.

#### Cost and cost-effectiveness analysis

We will adopt a mixed-methods approach to cost and economic evaluation to obtain a comprehensive understanding of the resources required to implement *RR *and economic consequences not captured solely using quantitative methods [61].

*Cost Analysis. *For each personnel-related cost, we will determine hourly wage + fringe based on national or state-level sources such as Bureau of Labor Statistics data and multiply that by time for each activity across phases [81]. We make needed adjustments for inflation and discounting, as applicable and characterize geographic variation in prices, as needed [55, 61]. We will generate descriptive statistics describing the base case (i.e., means) and variability in costs (i.e., standard deviations) for coaching and school-based teams. We will calculate total costs for each group coaching with school-based teams vs. coaching only. We will conduct sensitivity analyses to examine the robustness of our cost estimates and characterize uncertainty [56, 82]. We also will estimate costs in aggregate (e.g., societal) and by perspective group (e.g., school building), to provide tailored information on actual cost burden (and benefit) in implementing *RR*.

*Qualitative Analysis. *We will use qualitative data to expand and explain our quantitative findings. The qualitative data will be coded using directed content analysis – which makes use of existing frameworks to identify coding categories and derive the meaning of communications [83]. A codebook will be developed over multiple iterations via a close reading of the initial set of transcripts (i.e., inductive approach) [84], code generation, and group meetings. The codebook will include operational definitions of each code, examples of the code from the data, and guidance on when to use and not use the code. Two raters will code each transcript independently and resolve disagreements through consensus dialogue [85, 86]. Inter-rater reliability will be calculated using established Kappa statistic cutoffs (moderate: 0.40; substantial: 0.60; outstanding: 0.80) [87].

*Economic Evaluation. *We will determine cost-effectiveness of coaching with or without school-based teams [56, 88]. This will involve calculating a series of incremental cost-effectiveness ratios (ICERs) using implementation (fidelity, sustainment) and student outcomes (peer engagement; social network inclusion; social skills) as the effectiveness measures. The ICER represents the additional cost per unit improvement in the primary outcome (i.e., fidelity) achieved with coaching with school-based teams compared to coaching only. We will plot the ICER on a cost-effectiveness plane to illustrate the relationship between costs and effects. We will conduct deterministic (e.g., one-way) and probabilistic sensitivity analyses to examine how the ICER changes when varying key cost and effectiveness parameters within plausible ranges.

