#### Study purpose and aims

The purpose of this study is to test whether an educator-level implementation strategy, *coaching*, with or without a school-level implementation strategy, *school-based teams*, will maximize educators’ use (fidelity) of *RR* and student outcomes.

**Primary Aim 1:** Test the effect of coaching with school-based teams (vs. coaching only) on educators’ implementation and student social outcomes. We hypothesize that (a) coaching with school-based teams will result in greater *RR* fidelity (primary outcome) at the end of Semester 2 and sustainment the following school year, and (b) both arms will result in improved peer engagement and social skills from baseline to end of Semester 2, but coaching with school-based teams will improve student social network inclusion at the end of Semester 2 more than coaching.

**Secondary Aim 2: (Mediation)** Test the extent to which implementation leadership and climate will mediate the effect of coaching with school-based teams vs. coaching only on implementation and student outcomes. We anticipate that both implementation leadership and climate will mediate the relationship between coaching with school-based teams and coaching only and *RR* fidelity and student social outcomes at the end of Semester 2.

**Secondary Aim 3: (Moderation)** Explore if subgroups of students will benefit more from *RR *implementation by examining whether child-level characteristics (e.g., age, gender, autism classification) moderate the effect of coaching with school-based teams vs. coaching only on implementation and student outcomes. Based on our previous research [46], we anticipate that younger vs. older, female vs. male, or allistic vs. autistic students in schools that receive coaching with school-based teams will have better student social outcomes compared to coaching only.

**Secondary Aim 4**: Estimate the incremental costs of coaching with school-based teams versus coaching only to determine the most cost-effective approach.

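### The Economic Evaluation plans ICERs on five outcomes but defines the ICER on fidelity alone, and it judges uncertainty by the spread of a ratio whose denominator may be near zero for at least two of them

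*Protocol article*

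**What the plan says.** Secondary Aim 4 (Study purpose and aims) is worded as a choice: "Estimate the incremental costs of coaching with school-based teams versus coaching only to determine the most cost-effective approach".

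The Economic Evaluation paragraph (Cost and cost-effectiveness analysis) announces a series of ratios: "This will involve calculating a series of incremental cost-effectiveness ratios (ICERs) using implementation (fidelity, sustainment) and student outcomes", the latter being peer engagement, social network inclusion and social skills. That makes five: two implementation outcomes and three student outcomes. The next sentence narrows this to one: "The ICER represents the additional cost per unit improvement in the primary outcome (i.e., fidelity) achieved with coaching with school-based teams compared to coaching only". The cost-effectiveness plane and the sensitivity analyses are then attached to the ICER in the singular. The latter include "probabilistic sensitivity analyses to examine how the ICER changes when varying key cost and effectiveness parameters within plausible ranges".

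Hypothesis (a) of Primary Aim 1 expects a team advantage on fidelity and sustainment. Hypothesis (b) separates the student outcomes. For two of them, "both arms will result in improved peer engagement and social skills from baseline to end of Semester 2". For the third, "coaching with school-based teams will improve student social network inclusion at the end of Semester 2 more than coaching". The Methods part of the Abstract draws the same line between the student outcomes. The Sample size section nevertheless powers a between-arm difference of 14% in time spent in joint engagement.

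**The concern.** There are two linked problems.

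- **The deciding measure is not fixed.** A series on five outcomes and a definition tied to fidelity are both stated, in adjacent sentences. If the five results point in different directions, the text does not say which one answers Aim 4.
- **The uncertainty method suits a ratio poorly.** An ICER is the cost difference divided by the effect difference. Where the effect difference may be small, as the stated hypotheses allow for peer engagement and social skills, draws of the effect fall on both sides of zero. The ratio then jumps between large positive and large negative values, and its spread says little about which strategy is preferable.

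At stake is whether districts considering scale-up can rely on the Aim 4 conclusion.

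**Working it through.** **No figure to reproduce.** The Economic Evaluation text states no probability, error rate or sample size. The check uses the power statements in the Sample size section.

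**Inputs.** Power is 80% and Type I error 5%; sidedness is not stated, so two-sided is assumed. The powered differences are 14 percentage points of time in joint engagement and 0.15 in the fidelity slope comparison.

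**Step 1: implied standard errors.** SE = powered difference / (1.960 + 0.842) = powered difference / 2.802.
- Peer engagement: 14 / 2.802 = 5.0 points.
- Fidelity: 0.15 / 2.802 = 0.054.

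**Step 2: chance that the estimate has the wrong sign.** If the true effect is a fraction f of the powered effect, this is Φ(−2.802 f). The SE cancels, so the result is the same for any contrast with this power.

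| True effect as fraction of powered effect | Φ(−2.802 f) |
|---|---|
| 1 | 0.3% |
| 0.5 | 8% |
| 0.25 | 24% |
| 0 | 50% |

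If the 5% were one-sided, the multiplier would be 1.645 + 0.842 = 2.487, giving Φ(−1.24) = 11% at half and Φ(−0.62) = 27% at a quarter.

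**Step 3: when a plausible range reaches zero.** If that range is a 95% interval, it includes zero whenever the estimate is below 1.960 / 2.802 = 70% of the powered difference. For peer engagement this is 0.70 × 14 = 9.8 points.

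**Step 4: what the ratio does there.** Write C for the cost difference. It is assumed positive, because teams are added to coaching that all schools receive and bring sessions of 45–60 minutes for several staff. An effect draw of +0.1 point gives an ICER of C / 0.1 = +10C per point; a draw of −0.1 gives −10C. The two draws differ by 0.2 points, which is 0.2 / 5.0 = 0.04 SE, yet the ratio moves by 20C. Incremental net benefit, INB(λ) = λ × effect difference − C, changes over the same two draws by only 0.2λ.

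A negative ICER is also ambiguous. It arises when teams cost more and do worse, and equally when they cost less and do better. Percentiles of a mixture of positive and negative ICERs therefore have no consistent ordering from good to bad.

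**Step 5: which outcomes are exposed.** For fidelity, sustainment and social network inclusion the plan states a team advantage. At the full powered effect for fidelity, a wrong sign is rare (0.3%). For peer engagement and social skills no advantage is stated, so the lower rows of the table are the relevant ones unless the 14-point difference used for power is what the investigators expect.

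**The case against.** The strongest reply is that the sentence defining the ICER on fidelity already supplies a lead measure, with the other four alongside. That reading is possible and the fix adopts it, but the text does not say it, and the sentence before it gives all five outcomes the same standing.

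Second, the hypotheses do not say that the arms improve equally on peer engagement and social skills, and the Sample size section powers a 14% difference in joint engagement. This stands. A near-zero denominator is a possibility that the hypotheses leave open, not the plan's stated expectation.

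Third, uncertainty is addressed: a cost-effectiveness plane shows cost and effect differences separately, so sign changes would be visible. This stands in part. The plane is given an illustrative role, while the probabilistic analysis is directed at the ratio. The lack of a willingness-to-pay threshold in an article is not counted as a fault, since it is commonly left to the full analysis plan.

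A reader might go further and infer that Aim 4 will be decided by whichever of five ICERs looks best, so that with no true effect at least one would favour teams 83–97% of the time. The documents do not support this:
- No rule says that any one favourable ratio decides the aim.
- The 83–97% is the chance that at least one of five null effect estimates is above zero, at assumed correlations of 0.5 down to 0. Over all correlations from 0 to 1 it is 50–97%, and the article gives no correlation between outcomes.
- A positive effect at higher cost favours teams only if the cost per unit is acceptable, so a positive ICER is not by itself a favourable one.

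**Conclusion.** The point holds as an internal inconsistency together with a poorly chosen uncertainty measure. Series and single ratio need to be reconciled. The spread of the ICER cannot support the choice in Aim 4 where the effect difference may be near zero. That situation is open for two of the five outcomes on the stated hypotheses, and arises for any outcome whose effect falls well short of the powered one: about 8% wrong-sign estimates at half the powered effect and 24% at a quarter.

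These percentages assume approximately normal estimates, two-sided 5% and the stated 80% power. They are general properties of such a contrast, not features found only in this trial, and for outcomes without a power statement they are indicative. The point concerns a secondary aim and does not affect the primary fidelity comparison.

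**What to change.** In the Economic Evaluation paragraph:

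1. State that the fidelity analysis is the base case for Aim 4 and that sustainment, peer engagement, social network inclusion and social skills are supportive.
2. Run the probabilistic analysis on incremental net benefit, λ × effect difference − cost difference, resampling schools because schools are randomized. Report it with intervals and an acceptability curve over a stated range of λ.
3. Keep the ICER as a descriptive point estimate.
4. For the supportive outcomes, show cost and effect differences side by side, and interpret no ratio where the interval for the effect includes zero.

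The cost is some wording and a modest amount of analysis on data already planned; no participants or measures are added. The Discussion reports no enrolment as of September 2024. The downside is that the conclusion becomes conditional on λ, so the article would report for which values of a unit of fidelity teams are worth their cost, not a single unconditional answer.
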